### Assessments

Patients in both the CBT and SL groups are assessed at three time points: at baseline (T1), at the end of the intervention at 8 weeks (T2) and at 20 weeks follow-up (T3). Participants will remain part of the study for 5 months. The psychological assessment will include collection of demographic information (e.g. age, marital status, work, educational level), MS disease characteristics (e.g. disease-modifying medications, type of MS) and psychiatric history, completion of an online study questionnaire housed on a Research Electronic Data Capture (REDCap) online system on a secure server, administration of the BICAMS [26], completion of an online cognitive task, conduction of the SCID-5-RV [27] and Serum and Saliva collection. The treating psychologists and trial manager will be unblinded to the intervention. Assessments take may take up to 2 h to complete.

### Randomisation

Randomisation with permuted blocks of different sizes into the tailored CBT intervention and SL arms (1:1 ratio) will be undertaken via a secure, web-based Electronic Case Report Form (ECRF) system. The randomisation will be stratified by depression severity (mild and moderate depression classified using the BDI-II). Randomisation takes place after baseline assessment data has been collected. The randomisation table was created by an independent statistician and is concealed from study investigators and the assessment psychologists. Figure 1 shows the study CONSORT flow chart of participants in this trial. The trial manager will log into the ECRF system that will randomise participants into intervention group and will notify the treating psychologist about intervention allocation for the participant.

### Blinding

The clinical psychologist and registrar undertaking the baseline and outcome assessments will be blinded to participants’ treatment allocation.

### Interventions and treatment protocol

Participants will be randomised to either the CBT or the SL intervention. For both interventions, participants will attend weekly therapy sessions over an 8-week period. The first session will be 90 min long; the remainder sessions will be 60 min. All sessions will be face to face and will be undertaken in a consultation room in the RMH. Both interventions will be carried out in accordance with written and structured manuals. Participants will be issued with either a CBT or an SL client manual in their first session. The CBT and SL interventions will start within 1 week post-randomisation.

#### Tailored cognitive behavioural therapy

The aim of the tailored intervention is to significantly decrease levels of depression (primary outcome), anxiety (secondary outcome) and fatigue and pain impact and see improvements in levels of quality of life, fatigue and pain impact, sleep difficulties, MS illness acceptance, active coping skills, social support and resilience (tertiary outcomes). The tailored CBT intervention is derived from Beck’s cognitive theoretical model for the treatment of depression in adults [28]. Table 1 provides an overview of the modules included in the tailored CBT intervention.

**Table 1 Tab1:** Overview of the eight modules included in the tailored CBT intervention

	Title and description	CBT strategies
Module 1	Introduction to the tailored CBT program	Psycho-education on CBT model for treatment of depression and anxiety, fatigue and pain management, sleep hygiene; the link between thoughts, emotions, and behaviour; self-assessment activity identifying depressive, anxiety and MS symptoms; introduction to grief and loss model and acceptance of MS illness; self- assessment of stage of grief/loss; introduction of thought monitoring forms and provision of psycho-educational reading materials on depression, anxiety and MS and adjusting to living with MS
Module 2 and Module 3	Managing depressive and anxiety symptoms	Assist client to identify link between trigger events, thoughts, emotions and behaviour; identify situations that trigger low mood and anxiety; introduction to unhelpful thinking styles and how they contribute and maintain low mood and anxiety; introduce and discuss behavioural activation strategies such as pleasant activity scheduling including physical activity; mindfulness-based controlled breathing; progressive muscle relaxation to assist in the management of negative emotions; provide guided controlled breathing, progressive muscle relaxation and sleep hygiene audio tracks; provide psycho-educational material on the benefits of controlled breathing, progressive muscle relaxation and sleep hygiene
Module 4	Challenging unhelpful thoughts	Identifying own unhelpful thinking styles/errors using the thought monitoring form; discussion of how unhelpful thinking styles lead to negative emotions and unhelpful behaviours; introduction of how to manage and challenge unhelpful thoughts; finding alternative thoughts activity in session; provide psycho-educational material about challenging negative thoughts and coming up with alternative more helpful thoughts; provide thought monitoring, relaxation and pleasant activities forms for homework
Module 5	Managing fatigue and pain	Understanding pain and fatigue in MS from a cognitive behavioural perspective; discussion of pain and fatigue “traps”; provide psycho-educational material on fatigue and pain and depression cycle; identification of individual fatigue and pain cycle; identification of negative thoughts; identifying unhelpful thinking styles related to fatigue and pain; identification and discussion of more helpful thoughts
Module 6	Sleep hygiene	What is good sleep hygiene? Discussion of strategies to improve sleep such as establishing good sleep habits; provide psycho-educational material around factors that influence sleep
Module 7	Problem solving	Introduction to problem solving; discussion of how to problem solve in session using a client’s example; provide psycho-educational reading material on problem solving
Module 8	Relapse prevention and preparing for the future	Recap on all homework exercises and strategies covered in the intervention; discussion around managing depressive and anxiety symptoms, fatigue, pain and sleep problems; identifying triggers and early warning signs of depression relapse; discussion of strategies that have helped client; completion of depression relapse prevention plan in session

#### Supportive listening

SL includes listening skills based on the theory and counselling technique of Carl Rogers [29]. Core listening skills such as paraphrasing, reflecting, summarising and asking open-ended questions are employed. The aim is to provide the participants the opportunity to talk and express themselves in a non-judgmental, safe environment in which they experience empathy from the therapist and feel listened to. Sessions in the SL group are not structured. Participants can choose topics to discuss with their psychologist which they think are currently relevant to them. Figure 2 displays the SPIRIT schedule of enrolment, interventions and assessments.

**Fig. 2 Fig2:**
[figure not shown]
SPIRIT schedule of enrolment, interventions and assessments. *CBT* cognitive behavioural therapy, *SL* supportive listening, *SCID-5-RV* Structured Clinical Interview for DSM-5 Research Version, *BICAMS* Brief International Cognitive Assessment for MS, *BDI-II* Beck Depression Inventory-II, *STAI* State Trait Anxiety Inventory, *MFIS-5* Modified Fatigue Impact Scale-5 item version, *PES* Pain Effects Scale, *MS-QOL* multiple sclerosis-related quality of life measure, *WOC* 66 -item Ways of Coping questionnaire, *ACHCS* Acceptance of Chronic Health Conditions Scale, *RSA* Resilience Scale for Adults, *PSSS* Perceived Stress Scale, *TAQ* Therapeutic Alliance Questionnaire, *TSQ* Therapy Satisfaction Questionnaire

#### Training and supervision of therapists providing the interventions

Therapists will be registered clinical psychologists and registrars with training in CBT. All therapists will complete a 2-day workshop during which they will receive training in the two therapy techniques, with a day devoted to each of the CBT and SL interventions. All therapists will follow strict manualised protocols under the supervision of the trial manager.

#### Standardisation of the intervention

Standardisation of the intervention will be achieved by (1) use of a detailed intervention protocol which includes a therapist and client manual; (2) external monitoring of protocol compliance with routine feedback, through weekly supervision by the trial manager with the treating psychologists; (3) a protocol reminder system on our web-based data entry and management tool; and (4) a Data Safety and Monitoring Committee (DSMC) who will review protocol compliance. The DSMC will comprise an independent psychologist, neurologist and statistician who will be in contact with the principal researcher and trial manager.

#### Treatment fidelity

All intervention sessions will be recorded and used in supervision to provide feedback to therapists and to ensure treatment fidelity. We aim to take a 25% sample of intervention sessions for those in the CBT and SL groups from participants who agree to be recorded based on a random sample generated from an algorithm that takes into account session number, therapist and patient gender. Quality of CBT and SL administered will be assessed using the Cognitive Therapy Rating Scale [30] and a Supportive Listening Rating Scale. In addition, therapists in each condition will be asked to keep a self-reported fidelity checklist of all sessions.

### Outcome measures

#### Primary outcome measure

The primary outcome is the percentage of participants achieving the clinically meaningful change of 10 points or more on the BDI-II between baseline and post-intervention in the CBT intervention. Level of depression will be measured with the BDI-II.

#### Secondary outcome measures

Secondary outcomes are the magnitude of change between baseline and 20 weeks on the BDI-II in the CBT intervention with the level of depression measured with the BDI-II and the magnitude of change between baseline and post-intervention on the STAI. Level of anxiety will be measured with the STAI.

#### Tertiary outcome measures

Tertiary outcomes are the magnitude of change between baseline and post-intervention on fatigue and pain impact, MS-related quality of life, sleep quality, MS diagnosis acceptance, active coping styles, resilience and perceived social support in the early CBT intervention. Fatigue impact will be measured with the Modified Fatigue Impact Scale-5 item version (MFIS-5) [31]. Pain impact will be measured using the 6-item Pain Effects Scale [31]. Sleep quality will be measured with the Pittsburgh Sleep Quality Index [32]. MS-related quality of life is measured using the 54-item MS-related quality of life measure [33]. Coping styles will be examined using the 66-item Ways of Coping questionnaire [34]. Acceptance of MS illness will be measured using the 10-item Acceptance of Chronic Health Conditions Scale [35]. Level of resilience will be measured with the 33-item Resilience Scale for Adults [36], and Perceived Social Support will be measured using the 12-item Scale of Perceived Social Support [37].

#### Process measures

The Therapeutic Alliance Questionnaire [38] will be given to participants at each session, and they will be asked to complete and place it in an envelope which will be given to the therapist the following week. At post-intervention we will ask participants to complete a Therapy Satisfaction Questionnaire to provide information about the acceptability of the CBT intervention.

#### Saliva and serum samples

Participants will be asked to provide serum samples at baseline, post-intervention (8 weeks) and at 20 weeks follow-up. Additional consent for their use in future related research will be obtained.

#### BICAMS

We will collect test-retest reliability data for BICAMS from all participants enrolled in the trial. Participants will complete the BICAMS at the baseline assessment and again 1 week after this and prior to commencing their first therapy session. Additional consent for this data to be used in future related research will be obtained.

#### Sample size calculation

The current study is powered for the primary outcome of the proportion of patients who achieve a clinically significant change of 10 points or more on the BDI-II between baseline and post-treatment in the CBT intervention compared to those receiving the SL intervention. Based on pilot data by [name] and colleagues [2], the current study will aim to recruit 30 participants in each treatment arm (CBT and SL). The pilot results also revealed that 33% of newly diagnosed individuals screened did not meet eligibility to participate in the trial. Therefore, the current study will aim to screen 90 patients newly diagnosed with MS across three MS clinics in three hospital sites and via advertisements in order to obtain a total sample size of 60. This number will yield 90% power using an α = 0.05 threshold to observe a conservatively estimated 45% difference in proportion of patients achieving a favourable primary outcome. The sample size has also been inflated for drop-outs throughout the 20-week follow-up study.

### Planned statistical analysis

#### Effectiveness analysis

The primary outcome analysis will be an intention-to-treat between-group comparison of the proportion of patients who achieve a clinical and meaningful change of 10 points or more on the BDI-II between baseline and post-intervention adjusted for baseline depression severity using a logistic regression model. Baseline characteristics will be presented by randomised group without formal statistical tests. Secondary and tertiary outcome analyses will be undertaken using appropriate regression models adjusted for baseline depression severity. Longitudinal changes will be examined using regression models. No formal interim analyses for either efficacy or safety are planned, but safety outcomes will be continuously monitored.

#### Health economics evaluation

Participants will be asked to record service use including all types and duration of hospital admissions, frequency of outpatient hospital appointments, MS-related community service use, anti-depressant and anti-anxiety medication use and cost and paid and unpaid work using the Client Service Receipt Inventory [39]. Health-related quality of life data and quality-adjusted life years (QALYs) will be assessed using the health-related quality of life measure (EuroQoL-5D) [40].

#### Trial monitoring and management and patient safety

The study will be co-ordinated by a trial manager who will be a clinical psychologist. Trial monitoring and management will be undertaken by (1) a steering committee who will meet once a year to discuss the overall conduct of the trial and will include the lead investigator and key investigators from the recruitment sites, the trial manager and the statistician; (2) a management committee who will meet fortnightly to monthly to discuss recruitment issues and will include the trial manager and the key investigators from the hospital sites; and (3) safety monitoring, as performed by the independent DSMC who will provide advice regarding the safety of the trial to the steering committee and will consist of a clinician, a psychologist and an independent statistician. We will continuously monitor serious adverse events. All adverse events will be prospectively classified as serious or not serious. An independent clinical adjudication committee adjudicates all serious adverse events for this trial for subsequent reporting to the DSMC. In the unlikely case of an adverse event, this will be documented by the principal researcher and trial manager. Precautions have been taken to reduce the likelihood of adverse events occurring such as the exclusion of patients who are acutely suicidal or severely depressed. The interventions are delivered by clinical psychologists or registrars under the weekly clinical supervision of the trial manager. In the case of any adverse events as a result of taking part in either of the interventions, participation in the trial will be discontinued. Serious adverse events will be reported to the ethics committee. Any adverse events will be reported in the trial paper.

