**Methods:**

ACTION-MS is a two-arm parallel group, assessor-blinded, active comparator, randomised controlled trial which will test whether a tailored CBT-based intervention compared to an SL intervention can reduce depression and related factors such as anxiety, fatigue, pain and sleep problems in those newly diagnosed with MS. Sixty participants who are within 5 years of having received a diagnosis of MS and scored within the mild to moderate range of depression on the Beck Depression Inventory (BDI-II) will be recruited from MS clinics located across three hospital sites in Melbourne, Australia. The primary outcome is depression severity using the BDI-II at post-assessment. Intervention satisfaction and acceptability will be assessed. A cost-effectiveness analysis will also be conducted. Data will be analysed on an intention-to-treat basis.

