#### Withdrawal procedures

Participants will have the option to withdraw at any time during the study period of 5 months. The participant will need to request this formally, and the reason for withdrawing from the study will be recorded by the trial manager. Participant data collected prior to the withdrawal will be used with the permission of the participant. A participant can be withdrawn by the chief investigator should the need arise throughout the study period, and this will also be recorded.

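### A treatment-related adverse event ends trial participation, not only therapy, so outcomes can be lost because of harm and the intention-to-treat comparison is open to bias

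*Protocol article*

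**What the plan says.** The rule is one sentence in the protocol article, section Trial monitoring and management and patient safety: "In the case of any adverse events as a result of taking part in either of the interventions, participation in the trial will be discontinued".

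The same section says "All adverse events will be prospectively classified as serious or not serious", but the discontinuation rule makes no use of that classification. On frequency and handling it says "In the unlikely case of an adverse event, this will be documented by the principal researcher and trial manager". Serious events go to an independent adjudication committee and from there to the DSMC.

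Assessments sets three time points: baseline (T1), end of intervention at 8 weeks (T2) and follow-up at 20 weeks (T3). It describes participants as staying in the study for five months, a period that covers all three.

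On the analysis, Effectiveness analysis says "The primary outcome analysis will be an intention-to-treat between-group comparison of the proportion of patients" reaching a BDI-II change of at least 10 points from baseline to post-intervention. The Methods part of the abstract says "Data will be analysed on an intention-to-treat basis".

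Withdrawal procedures says "Participant data collected prior to the withdrawal will be used with the permission of the participant". It also lets the chief investigator withdraw a participant. It does not mention assessment after either kind of withdrawal.

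**The concern.** Stopping a treatment and leaving a trial are different events. An intention-to-treat comparison of randomised groups needs outcomes from patients who stop treatment as well as from those who finish it. Here the protocol itself removes patients from the trial, and the trigger is harm attributed to the treatment being compared. In a depression trial, such harm could plausibly be related to whether the BDI-II improves, and it could differ between CBT and supportive listening. The missing outcomes could then be informative and unequal between arms.

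The trigger is also broader than safety requires. A mild, non-serious related event that would not call for stopping therapy still takes the patient out of the trial. The rule depends on judging an event to be caused by the intervention, and the trial manager, who documents adverse events together with the principal researcher, is unblinded according to Assessments.

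At stake is the validity of the primary comparison with 30 patients per arm, where each lost patient is 1/30 = 3.3% of an arm. Safety oversight is not in question.

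**Working it through.** **1. What the text implies for the data**

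- Rule: any intervention-related adverse event, serious or not, in either arm, ends participation in the trial.
- Schedule: T2 at 8 weeks gives the primary outcome; T3 at 20 weeks gives the secondary BDI-II outcome.
- Event before week 8: neither T2 nor T3 is obtained, so the primary outcome is missing.
- Event between weeks 8 and 20: the primary outcome is kept and T3 is missing.
- Withdrawal procedures covers only data already collected, so it does not restore either assessment.

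The article separates therapy from trial elsewhere: Participant adherence defines adherence to CBT by sessions attended, while Assessments describes being in the study as the whole five months. Read in that light, the wording covers the assessments too.

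**2. The plan's own sample size**

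Inputs from Sample size calculation: 30 per arm, 90% power, α = 0.05, difference of 45 percentage points. Arm rates and sidedness are not given. I assume a two-sided test and vary the supportive listening (SL) rate from 5% to 50%.

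n per arm = [z₀.₉₇₅ √(2p̄(1−p̄)) + z₀.₉₀ √(p₁(1−p₁) + p₂(1−p₂))]² / (p₁−p₂)²

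- Largest requirement, at 72.5% v 27.5%: [1.960 × √0.5 + 1.282 × √0.39875]² / 0.45² = 23.8, so 24.
- Over the whole range, 19 to 24 per arm are needed, or 23 to 29 with continuity correction.
- 24/(1 − 0.20) = 30, if drop-out is assumed to be 20%.

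So 30 per arm reproduces. With 27 per arm, power is still 93 to 98% by the normal approximation. By Fisher's exact test it is 87 to 94% for SL rates of 10%, 20% and 27.5%. Losing a few patients matters mainly through bias, not power.

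**3. Illustration of bias in one arm**

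All counts are assumed. True response is 15/30 (50%), and k patients are discontinued before week 8.

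| k | Left out, all non-responders: 15/(30−k) | Left out, all would have responded: (15−k)/(30−k) | Counted as non-response, all would have responded: (15−k)/30 |
|---|---|---|---|
| 1 | 15/29 = 51.7% | 14/29 = 48.3% | 14/30 = 46.7% |
| 2 | 15/28 = 53.6% | 13/28 = 46.4% | 13/30 = 43.3% |
| 3 | 15/27 = 55.6% | 12/27 = 44.4% | 12/30 = 40.0% |

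Leaving the patients out shifts the arm by 1.7 to 5.6 points in either direction. Counting them as non-responders gives no error if they were non-responders, but an error of −3.3 to −10.0 points if they would have responded.

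**4. Illustration of bias in the difference (CBT minus SL)**

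Again with assumed rates, 30 per arm, and k non-responders left out of one arm only.

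| True rates | Arm losing patients | k = 1 | k = 2 | k = 3 |
|---|---|---|---|---|
| 65% v 20% (45.0 points) | CBT: 19.5/(30−k) − 6/30 | 47.2 | 49.6 | 52.2 |
| 65% v 20% (45.0 points) | SL: 19.5/30 − 6/(30−k) | 44.3 | 43.6 | 42.8 |
| 40% v 40% (0 points) | CBT: 12/(30−k) − 12/30 | 1.4 | 2.9 | 4.4 |

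Equal losses do not always cancel. With three non-responders left out of each arm, true rates of 15/30 in both arms give 15/27 − 15/27 = 0. True rates of 18/30 and 9/30 (30.0 points) give 18/27 − 9/27 = 33.3 points.

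**The case against.** The strongest reply is that the authors probably meant stopping therapy. The sentence follows one on how the interventions are delivered and supervised, and the article condenses a fuller protocol (version 1, 14 June 2016) that is not shown and may provide for follow-up after discontinuation. This lowers confidence but does not remove the point. The article states a rule, and its words end trial participation. If only therapy was meant, the sentence needs correcting, because staff who follow it literally would stop the assessments.

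The second reply is that the effect is likely to be small. Only events caused by a talking therapy count, the section calls adverse events unlikely, and acutely suicidal or severely depressed patients are excluded. The route to losing T3 alone needs an event attributed to therapy that has already ended. The largest complete-case shift in the one-arm illustration, 5.6 points, is below the standard error of a difference at 30 per arm, √(2 × 0.5 × 0.5/30) = 12.9 points at an assumed 50% response, and far below the 45-point target. All of this stands, and it limits how serious the point is. It does not justify a loss that is avoidable and tied to harm.

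Third, the sample size is said to allow for drop-out, and missing-data rules belong to an analysis plan that is not shown. The allowance protects power, not validity. A plan can impute a score but cannot recover one that the protocol stopped collecting.

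Fourth, Withdrawal procedures opens a parallel route through withdrawal by the chief investigator. That is fair, and the fix should cover it.

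**Conclusion.** The concern holds. As written, the protocol ends trial participation after any intervention-related adverse event, serious or not, and provides for no assessment afterwards. Outcomes would be missing because of treatment harm, which sits badly with the intention-to-treat comparison that the same document promises.

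Size and direction are unknown. The document gives no event rate, arm split, timing or missing-data rule. On the assumption of one to three losses before week 8, all with the same outcome, one arm of 30 at 50% shifts by 1.7 to 5.6 points under complete-case analysis. With no true effect, at 40% response in both arms, one to three CBT non-responders left out produce a false difference of 1.4 to 4.4 points. If no related event occurs, there is no bias.

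This should be fixed because the loss is avoidable and the remedy is cheap, not because a large bias has been shown. Confidence is moderate, since the authors may have intended something narrower than they wrote.

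**What to change.** Replace the sentence in Trial monitoring and management and patient safety with wording to this effect: after an adverse event judged to result from either intervention, the intervention is stopped where clinically indicated; the participant stays in the trial, and the 8-week and 20-week assessments, at minimum the BDI-II, are completed unless the participant withdraws consent to follow-up.

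Apply the same follow-up rule to withdrawals by the chief investigator under Withdrawal procedures. The clause there on permission to use data already collected can stay as it is.

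A sensitivity analysis that counts primary outcomes missing after a related adverse event as non-response would be a useful addition. It is optional and belongs in the analysis plan. It can itself bias an arm downwards, as the last column of the one-arm table shows.

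The cost is a protocol amendment and a few additional assessments. A full visit may take up to 2 hours; the BDI-II alone is the minimum. When the article appeared in January 2020, recruitment was expected to run until December 2021 and data collection until April 2022, so an amendment at that point could still have protected outcomes.
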